### Sample size {14}

A total of 600 newborns will be recruited. For the primary outcome, we predict raised AGP (> 1 g/L) in 35% infants at age 6 months in the control group [22]. The study requires a total of 524 infants (131 per am) to demonstrate a 50% reduction (relative risk = 0.50) in the prevalence of the primary outcome from 35% in the control arm to 17.5% in any of the intervention’s arms with 80% power and *α* = 0.0167. The alpha of 0.0167 is required to allow for three comparisons, one for each intervention arm, against the control arm. We will recruit 150 infants per group to allow for 13% dropouts.

We have used AGP concentration as a dichotomous outcome as a conservative approach as we wish to recruit sufficient numbers of children to compare other important biomarkers between groups. Using values of biomarkers as continuous variables will increase the power of the study to detect differences between the study arms. Using AGP as an example, we predict a mean log_10_ value of − 0.24 g/L in controls based on data from Zimbabwe [20]. In total, 102 infants in the intervention and the control group are required to show that mean AGP concentration is 20% lower in the intervention compared with the control group with 90% power at the 5% significance level.

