## Statistical methods

### Statistical methods for primary and secondary outcomes {20a}

Demographic, clinical and laboratory data and also variables reflecting feeding, WASH practices and environmental factors will be summarised using simple descriptive statistics. Continuous variables will be summarised according to the number of subjects with non-missing data as mean, standard deviation, median, minimum and maximum. Categorical variables will be summarised according to the absolute frequency and percentage of subjects in each category level. The denominator for the percentages is the number of subjects with data available unless noted otherwise.

The primary outcome analysis will be based on the intention-to-treat (ITT) population which will include all randomised study subjects. The proportion of infants aged 6 months with abnormal AGP concentration (> 1 g/L) in each intervention arm will be compared with the proportion in the control arm. Data will be analysed using generalised linear models with treatment as the only predictor, AGP concentration at baseline as covariate, binomial distribution and log link function, generating the estimates of treatment effects in relative risk and their 95% confidence intervals (CI). Covariate-adjusted analysis will also be performed with covariates that affect the primary outcome (e.g. season of birth, HIV exposure, mode of delivery, mode of feeding, exposure to antibiotics, WASH and environmental factors such as water source, sanitation facilities, hygiene practices, use of soap, number of siblings, proximity to animals). Subgroup analysis will also be performed on the covariates used in the covariate-adjusted analysis.

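### The trial is sized on a required alpha of 0.0167 for each of three primary comparisons, but the analysis section gives those comparisons only 95% confidence intervals and never carries the 0.0167 level forward

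*Protocol article*

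**What the plan says.** In the protocol article, Sample size {14} fixes the design level: "The alpha of 0.0167 is required to allow for three comparisons, one for each intervention arm, against the control arm". The same section states the target as "to demonstrate a 50% reduction (relative risk = 0.50) in the prevalence of the primary outcome". The risks it assumes are 0.35 for controls and 0.175 for an intervention arm, and the power is 80% at the 0.0167 level. The stated result is "The study requires a total of 524 infants (131 per am", followed by "We will recruit 150 infants per group to allow for 13% dropouts".

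Statistical methods for primary and secondary outcomes {20a} compares the proportion with raised AGP at 6 months in each intervention arm with that in the control arm. It uses a binomial model with log link, "generating the estimates of treatment effects in relative risk and their 95% confidence intervals (CI". It names no significance level, adjusted interval or multiplicity procedure for these comparisons. The later text of {20a}, and sections {20b} and {20c}, do not mention 0.0167 or any adjustment either.

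Two other statements bear on the point. Trial design {8} calls the study exploratory. Who will be blinded {17a} refers to a separate statistical analysis plan, to be signed off before the allocation sequence is released to the study team.

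**The concern.** The two sections attach different levels to the same three comparisons. The design calls 0.0167 required, yet the only inferential output specified for the primary analysis is an interval at a level equivalent to 0.05. This is more than a detail left to the analysis plan, because the article itself fixes a level for the primary intervals and it is not the design level.

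At stake is which product, if any, is said to reduce systemic inflammation. An arm with a p-value between 0.0167 and 0.05 has a 95% interval that excludes 1 and misses the threshold on which the trial was sized. A reader relying on {20a} could report benefit where a reader relying on {14} would not. The trial also recruits about a third more evaluable infants than a 0.05 level would need, to pay for error control that the analysis section does not mention.

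**Working it through.** **Inputs.** From {14}: control risk 0.35, intervention risk 0.175, power 80%, alpha 0.0167 per comparison, 131 evaluable infants per arm. From {16a}: allocation 1:1:1:1. From {20a}: three comparisons with one shared control, and 95% intervals. Sidedness is not stated and is inferred in step 1.

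**1. Reproduce the plan's figure.** For two proportions with pooled variance and no continuity correction:

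n = [z(1−α/2)·√(2·p̄·(1−p̄)) + z(0.80)·√(p₀(1−p₀) + p₁(1−p₁))]² / (p₀ − p₁)²

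- p̄ = (0.35 + 0.175)/2 = 0.2625, so √(2 × 0.2625 × 0.7375) = 0.6223.
- √(0.35 × 0.65 + 0.175 × 0.825) = √0.371875 = 0.6098.
- Two-sided α = 0.0167 gives z = 2.393; z(0.80) = 0.842.
- n = (2.393 × 0.6223 + 0.842 × 0.6098)² / 0.175² = 130.9, rounded up to **131 per arm**, or 4 × 131 = **524**. This matches exactly.
- With the same formula, one-sided 0.0167 gives 111, and two-sided 0.05 gives 99 per arm (396 in total). The design therefore uses two-sided 0.0167, and 131/99 = 1.32.

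**2. Level implied by the intervals.** A 95% interval uses z = 1.960, which is two-sided 0.05. The interval matching 0.0167 is a 98.33% interval with z = 2.393. The ratio 2.393/1.960 = 1.22, so it is about 22% wider on the log relative-risk scale.

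**3. Family-wise error over three comparisons.** With equal arms and a shared control, the pairwise correlation of the test statistics is (1/n)/(2/n) = 0.5. Simulation of three normal statistics with that correlation (4,000,000 draws) gives the second column. The bound is the sum of the three levels.

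| Level per comparison | Shared control | If independent | Upper bound |
|---|---|---|---|
| 0.05 (95% CI read as the test) | 12.5% | 1 − 0.95³ = 14.3% | 15% |
| 0.0167 (98.33% CI) | 4.5% | 1 − 0.9833³ = 4.9% | 5.01% |

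In the favourable direction only, the shared-control figures are 6.2% and 2.2%. Simulating binary data directly (131 per arm, common risk 35%, Wald intervals on the log relative risk, 1,000,000 trials) gives 11.7% and 4.0% two-sided.

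**4. How often the two levels disagree.** Power at 131 per arm and the design effect is 80.0% at 0.0167 and 90.1% at 0.05. The difference, 90.1 − 80.0, is about 10 percentage points. That is the chance, per arm, of a p-value between the two levels.

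**5. A worked case.** Take 46/131 events in control (35.1%) and 29/131 in an intervention arm (22.1%).

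- RR = 29/46 = 0.63, so ln RR = −0.461.
- SE = √(1/29 − 1/131 + 1/46 − 1/131) = 0.2024, and z = −2.28 (p = 0.023).
- 95% CI: exp(−0.461 ± 1.960 × 0.2024) = 0.42 to 0.94, which excludes 1.
- 98.33% CI: exp(−0.461 ± 2.393 × 0.2024) = 0.39 to 1.02, which includes 1.

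With 30 or 31 events the same split occurs (95% upper limits 0.96 and 0.99; 98.33% upper limits 1.05 and 1.08). With 28 events both intervals exclude 1, and with 32 both include it.

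**The case against.** **No decision rule is stated.** {20a} says that the models yield relative risks with 95% intervals. It does not say that an interval excluding 1 means success, and it does not mention a 0.05 test. A 95% interval is a common reporting format and can stand beside a test at 0.0167, the only alpha given for these comparisons. A reader might infer that the trial will test each arm at 0.05 with no adjustment and so run a 12.5% family-wise error. The document does not support that. The figure is conditional on the intervals being used as the tests. What remains is that the level called required is absent from the section that specifies the primary analysis, and a different level stands there.

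**The analysis plan may settle it.** {17a} shows that a plan is to be signed off before allocation is released, and it may well test at 0.0167. Leaving such detail to it is normal. This lowers the severity but does not remove the mismatch between two levels that the article itself states.

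**The trial is exploratory.** That weakens any general demand for strict family-wise control and counts against treating the point as critical. But {14} does not treat the adjustment as optional, and it sized the trial on it.

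**Bonferroni is not a fault.** A reader might also infer that the plan errs by ignoring the shared control. It does not: Bonferroni is valid under any dependence and is only slightly conservative here (4.5% rather than 5%). Holm or Dunnett would be a preference, not a correction.

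**Conclusion.** The mismatch is real and of moderate severity. The design level of 0.0167 drives the sample size, and the primary analysis section does not carry it forward, giving only intervals equivalent to 0.05 each. If those intervals are read as tests, two-sided family-wise error is about 12.5% (11.7% in the binary-data simulation) instead of at most about 5%. At the design effect, about one arm-versus-control comparison in ten would fall where the two sections can be read to opposite conclusions.

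These figures assume two-sided testing (inferred from the exact match to 131), 131 evaluable infants in every arm, and the planned risks of 35% and 17.5%. The sample size is correct as stated and is not in question. The document does not show that unadjusted testing is intended.

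**What to change.** In {20a}, and correspondingly in the analysis plan before allocation is released:

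- State that each of the three primary arm-versus-control comparisons is judged at two-sided 0.0167.
- Report 98.33% confidence intervals for the three primary relative risks.
- If 95% intervals are also shown, label them as descriptive.

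Holm or Dunnett may be named instead, but neither is needed. If Holm is chosen, 98.33% intervals should not be presented as the matching decision intervals. Holm tests the second and third ordered p-values at 0.025 and 0.05, so an arm can succeed while its 98.33% interval includes 1. In simulation with all three arms at 17.5% against 35% (131 per arm, 400,000 trials), at least one arm succeeds under Holm with p above 0.0167 in about 17% of trials. That would bring back the conflict this change is meant to remove.

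The cost is a few sentences and primary intervals about 22% wider on the log scale. Recruitment, data collection, the model and the point estimates are unchanged.

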#### Exclusion criteria

Multiple pregnancy (e.g. twin/triplets)Infant aged 4 days or olderSuspicion or presence of any acute illness (e.g. fever; receiving treatment with antibiotics)Congenital abnormality that might be life-threatening or impair growthInfant with potential contraindication to pro/synbiotics (e.g. suspected immune suppression; cardiac abnormality)Mother unlikely to stay in study area for the duration of the studyAny health staff or study staff concerns regarding safety to participate in the trial

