#### Details of pro/synbiotics

Labinic synbiotic: prebiotic (BENEO Orafti Synergy1; 50% oligofructose:50% FOS; 200 mg) + 3 live bacteria: *Lactobacillus acidophilus* NCFM, *Bifidobacterium infantis* Bi-26 and *Bifidobacterium bifidum* Bb-06; total of 5 billion organisms/day (https://biofloratech.com/EU_page_Labinic_Drops.html).Lab4b probiotic: 4 live bacteria: *Lactobacillus salivarius* CUL61, *Lactobacillus paracasei* CUL08, *Bifidobacterium animalis subspecies lactis* CUL34 and *Bifidobacterium bifidum* CUL20; total of 10^10^ organisms/day (https://www.lab4probiotics.co.uk/).Lab4b synbiotic: prebiotic (long-chain FOS 150 mg/day) + Lab4b probiotic.

All three supplements will be presented as powder inside capsules with one dose/capsule. In this open-label study, the colour of the capsules differs for each preparation to facilitate correct administration. The contents of the capsule can be sprinkled directly into the infant’s open mouth before feeding or mixed in a clean container with sterile water. The administration will be repeated once if the infant vomits within 30 min. All administration of supplements will be supervised by a member of the research team.

In infants taking antibiotics, including HIV-exposed infants taking co-trimoxazole daily from age 4–6 weeks, the supplements will be administered at least 4 h before/after the antibiotic or between doses to minimise the effect of the antibiotic on the microbes. We aim to start the interventions in infants within the first 3 days of birth to limit potential competition from other gut organisms against the probiotics.

Although the dietary supplements are stable at ambient temperatures below 25 °C for up to 2 years, viability at higher temperatures has not been assessed. Therefore, a cold chain was maintained during shipment of the supplements with storage at 5 °C ± 3 °C in Kenya and transfer to participants’ home in a cold box. Quantitative counts of the probiotics will be done at intervals during the study to confirm viability.

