### Relevant concomitant care permitted or prohibited during the trial {11d}

All participants will be offered routine care according to local and national policies. This includes all childhood vaccinations during infancy and advice regarding the importance of exclusive breast feeding, complementary feeding from age 6 months and sleeping under an insecticide-treated bed net. The study team will re-enforce these positive health messages where appropriate. All routine medications used for the treatment of childhood illnesses is permitted and concomitant medications taken during the study will be recorded with indications and dates of administration. No medications are prohibited. Study staff will facilitate referral to health services for infants who are unwell during scheduled and unscheduled study visits.

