### Participant timeline {13}

Pregnant women and families will be provided with information about the study when attending ANC during the third trimester. Following the delivery of a live infant, newborns will be assessed by study staff according to the inclusion/exclusion criteria within the first 3 days after birth. After securing informed consent, newborns will be allocated randomly to one of the 4 study arms. Study staff will undertake a Ballard assessment to determine gestation, measure anthropometric indices and record infant feeding, WASH practices and environmental information using standardised questionnaires. Study staff will confirm that the infant has taken at least one breastfeed well and then assist the mother/carer in administering the first dose of the appropriate dietary supplement in infants allocated to the active study arms.

Study staff will visit daily for the following 9 days and then weekly to age 6 months to supervise the administration of the pro/synbiotic to infants in the intervention arms. The same visit schedule will be applied to infants in the control arm (no dietary supplement). At all visits, research staff will encourage exclusive breastfeeding and other positive health practices and facilitate transport to the clinic as required in unwell infants. Follow-up visits for all participants to collect data and stool and blood samples will be scheduled for 6 weeks, 3 months, 6 months and 12 months. A final follow-up visit at 2 years will be scheduled to record long-term outcomes (Fig. 1).

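### The adjusted and subgroup analyses are not limited to pre-allocation covariates, so infant antibiotic use and, to a lesser degree, feeding mode could enter as post-randomisation variables

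*Protocol article*

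**What the plan says.** All of this is in the protocol article.

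- *Primary model* (Statistical methods {20a}): "generalised linear models with treatment as the only predictor, AGP concentration at baseline as covariate, binomial distribution and log link function". None of the covariates discussed here is in it.
- *Rule for the adjusted analysis* ({20a}): "Covariate-adjusted analysis will also be performed with covariates that affect the primary outcome". The examples include "mode of feeding, exposure to antibiotics, WASH and environmental factors such as water source, sanitation facilities, hygiene practices". No time of measurement is given.
- *Subgroups* ({20a}): "Subgroup analysis will also be performed on the covariates used in the covariate-adjusted analysis".
- *Entry conditions* (Eligibility criteria {10}): every infant must be breastfed. Acute illness is an exclusion, with "receiving treatment with antibiotics" as an example.
- *Enrolment record* (Participant timeline {13}): staff "record infant feeding, WASH practices and environmental information using standardised questionnaires". This is listed after allocation and before the first dose. Antibiotics are not among the items named.
- *Medication record* ({11d}): "concomitant medications taken during the study will be recorded with indications and dates of administration".
- *Hypothesis* (Secondary objectives): one objective is to find out whether supplementation lowers the number of illness episodes.

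**The concern.** A covariate that allocation can change is not a baseline covariate. If the supplements prevent illness, they may also prevent antibiotic courses. A model that holds antibiotic use constant then no longer estimates the total effect of supplementation on raised AGP, because it removes whatever part runs through avoided illness.

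Subgroups have the same difficulty. Infants who needed no antibiotics under supplementation need not be comparable with infants who needed none in the control arm, so randomisation no longer protects the comparison within that subgroup. A difference between subgroups could be read as effect modification when it only reflects who ended up in each group.

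The results at stake are the covariate-adjusted and subgroup estimates for the primary outcome. They are planned and will be reported beside the main result.

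**Working it through.** **1. The plan's own figure.** The sample size section gives 131 per arm for 35% versus 17.5%, α = 0.0167 and 80% power. With the two-sided pooled-variance formula, no continuity correction and a mean proportion of 0.2625:

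n = [2.393 × √(2 × 0.2625 × 0.7375) + 0.842 × √(0.35 × 0.65 + 0.175 × 0.825)]² / 0.175² ≈ 131.

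The figure reproduces. It does not depend on the covariates at issue.

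**2. When each covariate can vary.**

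| Covariate | At entry | Afterwards |
|---|---|---|
| Infant antibiotics | Current treatment is an exclusion; no enrolment record is described | Expected and recorded with dates |
| Feeding mode | All breastfed; exclusive versus mixed feeding may still differ; recorded at enrolment | Can change up to 6 months |
| WASH and environment | Recorded at enrolment | No effect of the supplements proposed |
| HIV exposure, season of birth, mode of delivery | Fixed | – |

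Only infant antibiotics, and partly feeding mode, would draw most of their variation from after randomisation.

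**3. Illustration for the adjusted analysis.** The total relative risk (RR) of 0.50 is the design value. Every other input is an assumption, because the documents give no antibiotic rates. Let p0 = 0.50 be antibiotic use in controls, p1 use in the supplemented arm, b the risk ratio for raised AGP associated with antibiotic use, and d the RR after adjustment. On a log-link model:

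0.50 = d × [1 + p1(b − 1)] / [1 + p0(b − 1)], so d = 0.50 × [1 + p0(b − 1)] / [1 + p1(b − 1)].

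- No change in use (p1 = 0.50), any b: d = 0.50.
- 20% fewer (p1 = 0.40), b = 1.3: 0.50 × 1.15 / 1.12 = 0.51.
- 20% fewer, b = 1.5: 0.50 × 1.25 / 1.20 = 0.52.
- 30% fewer (p1 = 0.35), b = 2: 0.50 × 1.50 / 1.35 = 0.56.
- 50% fewer (p1 = 0.25), b = 2: 0.50 × 1.50 / 1.25 = 0.60.
- As the last case, plus an unmeasured cause present in 30% of infants that raises both antibiotic use and raised AGP 1.5-fold (large-sample simulation): adjusted RR 0.61; 0.60 in antibiotic users and 0.62 in non-users.

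**4. Illustration for a subgroup.** Suppose there is no effect on AGP, 30% of infants are frail, and treatment lowers antibiotic use by 30% in everyone. If 80% of frail and 40% of other control infants receive antibiotics, the frail share of the no-antibiotic subgroup is:

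- controls: 0.30 × 0.20 / (0.30 × 0.20 + 0.70 × 0.60) = 0.060 / 0.480 = 12.5%;
- supplemented: 0.30 × 0.44 / (0.30 × 0.44 + 0.70 × 0.72) = 0.132 / 0.636 = 20.8%.

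If frailty doubles the risk of raised AGP, the subgroup RR is 1.208 / 1.125 = 1.07; if it triples it, 1.415 / 1.250 = 1.13. With antibiotic rates of 60% and 30% the values are 1.04 and 1.06; with 50% and 30% they are 1.02 and 1.04. The spurious effect depends heavily on rates nobody has stated.

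**The case against.** The strongest reply is that the protocol never says these are follow-up values. The covariates are an open list of examples in a condensed article, and measurement windows usually belong in the analysis plan. Feeding, WASH and environmental factors have an enrolment record before the first dose. The background section names maternal as well as infant antibiotics among the factors that disturb the microbiome, so antibiotic exposure could mean exposure around birth. Breastfed at entry does not mean exclusively breastfed, so feeding mode can vary at enrolment.

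Most of this stands, and it rules out three stronger readings.

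- A reader might infer that the plan knowingly adjusts away part of the effect. It does not say so. Bias also requires that treatment changes the covariate, which is plausible but undocumented.
- A reader might add hygiene practices to the problem. They have an enrolment value, visits and advice are the same in all arms, and no passage proposes that a supplement changes hygiene. The open-label design leaves only a small possibility.
- A reader might point to "In infants taking antibiotics, including HIV-exposed infants taking co-trimoxazole daily from age 4–6 weeks". Co-trimoxazole follows HIV exposure, which is the stratification factor, so that part of antibiotic exposure is not a consequence of allocation.

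The reply does not remove the core. The article goes beyond silence: it states a selection rule, names antibiotic exposure, and reuses the list for subgroups. The only antibiotic record it describes is of medication during the study. Followed as written, the rule admits infant antibiotic use after allocation.

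**Conclusion.** The point holds in a limited form. The rule for the adjusted and subgroup analyses allows post-randomisation covariates. Infant antibiotic exposure is the clear case and feeding mode a weaker one. If the supplements reduce antibiotic use and antibiotic use marks a higher risk of raised AGP, the adjusted estimate moves towards the null.

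The documents do not give the inputs needed to size this. In the cases tried, a true relative risk of 0.50 became 0.50 to 0.61, so the shift runs from nil to moderate. It is nil if treatment leaves antibiotic use unchanged. The upper end needs a halving of antibiotic use, a two-fold risk and a shared unmeasured cause.

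It would be wrong to infer that the trial's main result is compromised. The primary model holds only treatment and baseline AGP, and 131 per arm (150 recruited) stands. The trial is also described as exploratory. The change is still worth making, because the affected analyses concern the primary outcome and the remedy is nearly free.

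**What to change.** State in {20a}, and carry into the statistical analysis plan, that covariate adjustment and subgroups use only values fixed before allocation or recorded at enrolment before the first dose:

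- HIV exposure, season of birth and mode of delivery;
- maternal or peripartum antibiotics, where recorded;
- feeding, WASH and environmental factors from the enrolment questionnaire.

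The timeline lists that questionnaire after allocation, so name the enrolment values explicitly as the baseline.

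Report infant antibiotic courses and later feeding by arm in descriptive tables, or in an analysis labelled exploratory and non-causal. This agrees with {20b}, which already names HIV exposure and Caesarean delivery as subgroups.

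The cost is a sentence or two of wording. No new data, no extra recruitment and no change to the primary model are needed. If maternal antibiotics were not recorded, that covariate is left out.

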#### Secondary outcomes

Biomarkers at ages 6 weeks and 3, 6 and 12 months
Plasma marker of chronic inflammation: (AGP; at 6 weeks and 3 and 12 months)Stool biomarker of intestinal inflammation: myeloperoxidaseStool biomarker of intestinal permeability: α1-antitrypsin (AAT)Plasma marker of acute inflammation: C-reactive protein (CRP)Plasma marker of gut mucosal integrity: intestinal fatty acid-binding protein (IFABP)Plasma growth hormones: insulin-like growth factor (IGF)-1 and its carrier protein IGF-binding protein 3Stool pH

Clinical outcomes to age 2 years
MortalityHospital admissionAll-cause sick-child clinic visitsDisease-specific sick-child clinic visits (e.g. diarrhoea; respiratory and skin infections)Anthropometric outcomes: weight, length, mid-upper arm circumference (MUAC), head circumference

Feeding and WASH practices and environmental factors that may influence the development of the gut microbiome will be assessed by questionnaires.

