Laboratory assays will be carried out according to the manufacturer’s instructions. All assays will be carried out in duplicate and repeated should there be a discrepancy in values. Processing, analysis and storage of samples will be undertaken at the Research Laboratories at the Kenya Medical Research Institute (KEMRI) Centre for Global Health Research, Kisumu, Kenya.

Clinical outcomes will be assessed as follows:
Mortality and hospital admissions will be recorded by a questionnaire applied during each scheduled and unscheduled visit and information copied from any health cards carried by the mother/carer and/or from hospital records and reported as serious adverse events (SAEs).Episodes of all-cause and disease-specific sick-child clinic visits will be recorded during each scheduled visit as reported by the mother/carer and information copied from any health cards carried by the mother/carer and/or from clinic records.Weight will be measured to the nearest 100 g using electronic scales. MUAC will be measured at the mid-point between the tip of the shoulder and the tip of the elbow using a non-stretchable MUAC tape to the nearest 0.1 cm. Length will be measured to the nearest 0.1 cm using a length board. Head circumference will be measured to the nearest 0.1 cm using a non-stretchable tape measure. All measurements will be performed in duplicate and a third measurement made should values disagree by a pre-specified amount. Scales and length boards will be checked daily for accuracy using a standard weight and a ruler.

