Analysis of the secondary endpoints with single measurements will also be presented in the ITT and per-protocol (PP) populations and in a similar fashion as for the primary endpoint analysis using generalised linear method. The PP population will be all randomised study subjects who complete 75% or more of the supervised doses. For continuous outcomes, normal distribution and identity link function will be used, from which mean difference together with its 95%CI will be derived. Generalised linear mixed model (GLMMIX) will be employed for the analysis of secondary outcomes with repeated measurements. The GLMMIX model will have treatment, visit, interaction between treatment and visit as fixed effects, baseline measurement of an outcome as covariate, and subject as random effect. The treatment difference between two treatment arms at each visit together with its 95% confidence interval will be derived from the GLMMIX model. Missing data will be treated as missing completely at random in the GLMMIX model analysis and no imputation of primary or secondary endpoints will be made. For the analysis of binary secondary outcomes with repeated measurements, the GLMMIX model will have a binomial distribution and logit link function. The odds ratio between two treatment arms at each visit together with its 95% confidence interval will be derived from the GLMMIX model. For the analysis of continuous secondary outcomes with repeated measurements, the GLMMIX model will have a normal distribution and identify link function. The mean difference between two treatment arms at each visit together with its 95% confidence interval will be derived from the GLMMIX model.

For anthropometric outcomes, *z* scores will be calculated using the WHO Anthro Survey Analyser and WHO 2006 child growth standards [47]. Analyses will include both the comparison of anthropometric indices between intervention groups at different time points and also growth expressed as change in indices over time.

Analyses of the potential adverse effects of the dietary supplements will be done in the safety population.

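### Mortality falls by category under the primary outcome's log-binomial relative risk, which has no finite log estimate when an arm has no deaths, and no exemption is made for rare outcomes

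*Protocol article*

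**What the plan says.** Mortality heads the list in the Secondary outcomes section under "Clinical outcomes to age 2 years". It is binary and can occur only once per child, so it is not a repeated measurement. On how it is captured, Plans for assessment and collection of outcomes {18a} says: "Mortality and hospital admissions will be recorded by a questionnaire applied during each scheduled and unscheduled visit". The same sentence provides for reporting deaths as serious adverse events.

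Statistical methods {20a} does not name mortality. It sets a rule by type of outcome: secondary endpoints with single measurements are analysed, in the ITT and per-protocol populations, "in a similar fashion as for the primary endpoint analysis using generalised linear method". The primary model is specified as "binomial distribution and log link function, generating the estimates of treatment effects in relative risk and their 95% confidence intervals (CI". Two departures are written in:

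- "For continuous outcomes, normal distribution and identity link function will be used".
- Outcomes with repeated measurements go to a generalised linear mixed model.

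Nothing is said about sparse or zero events, or about whether tests and intervals are Wald, likelihood-ratio or exact. The same section also provides for description: "Categorical variables will be summarised according to the absolute frequency and percentage of subjects in each category level". On harms it says: "Analyses of the potential adverse effects of the dietary supplements will be done in the safety population", without giving a method.

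**The concern.** The log-binomial relative risk was chosen for an outcome expected to be common: "we predict raised AGP (> 1 g/L) in 35% infants at age 6 months in the control group". The same rule then covers deaths, which may be few or absent in an arm of 150. With no deaths in an arm, the estimated relative risk is zero or undefined, its logarithm is not finite, and the maximum likelihood estimate on the model's scale does not exist. Standard software still prints a coefficient, a very large standard error and a Wald p-value close to 1.

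At stake is the model-based comparison of deaths. Mortality is a listed secondary outcome, and the Discussion says that, to the authors' knowledge, these probiotics formulated as synbiotics have not been used in this setting before. A p-value that stays near 1 however many deaths occur in the other arm is a poor summary of such a comparison.

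**Working it through.** **Inputs from the protocol article.** Sample size {14}: 150 recruited per arm, 131 per arm required, 35% against 17.5%, alpha 0.0167, power 80%. Sequence generation {16a}: 1:1:1:1. **Assumed:** mortality, since the article gives no rate; 0.5% to 5% is shown.

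**1. The plan's own figure.** Two-sided, pooled variance, no continuity correction:

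n = [z(1−α/2)·√(2·p̄·(1−p̄)) + z(0.80)·√(p1(1−p1) + p2(1−p2))]² / (p1−p2)²

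With p̄ = 0.2625, this is [2.393 × 0.622 + 0.842 × 0.610]² / 0.175² ≈ 131 per arm, 524 in total. The stated figure reproduces. It concerns the 35% outcome only and says nothing about deaths.

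**2. Chance of an arm without deaths.** For one arm: q = (1−p)^150. For at least one of four arms with the same p: 1 − (1−q)^4.

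| Assumed mortality | Given arm empty | At least one of four empty |
|---|---|---|
| 0.5% | 47% | 92% |
| 1% | 22% | 63% |
| 1.5% | 10% | 35% |
| 2% | 4.8% | 18% |
| 3% | 1.0% | 4.1% |
| 5% | 0.05% | 0.2% |

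If the empty arm is the control, none of the three contrasts has a finite relative risk.

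**3. What the model reports for 0/150 against 6/150.**

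- Log-binomial fit, Wald: log relative risk about −22, standard error about 16,000, p = 0.999, interval effectively unbounded.
- Fisher's exact test: 2 × C(150,6)/C(300,6) = 0.030.
- Score test: z = (6/150)/√(0.02 × 0.98 × 2/150) = 2.47, p = 0.013.
- Likelihood-ratio test, same model: log-likelihood −25.19 with separate risks and −29.41 with a common risk; 2 × 4.22 = 8.44 on 1 df, p = 0.004. The upper 95% profile limit for the relative risk is 0.37.

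The Wald p stays at 0.999 from 0 against 3 up to 0 against 10. Fisher's p is below 0.05 from 0 against 6 (0.030) and below 0.0167 from 0 against 7 (0.0145).

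**4. How often this would hide a difference.** It needs an empty arm and at least 6 deaths in the arm compared with it. For one contrast the probability is P(no deaths in the intervention arm) × P(at least 6 in control):

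| True risk, control vs intervention | Probability |
|---|---|
| 2% vs 0.5% | 0.471 × 0.082 = 3.9% |
| 3% vs 1% | 0.221 × 0.296 = 6.6% |
| 4% vs 1% | 0.221 × 0.558 = 12% |
| 4% vs 0.5% | 0.471 × 0.558 = 26% |
| 4% vs 2% | 0.048 × 0.558 = 2.7% |
| 2% vs 2% | 0.048 × 0.082 = 0.4% |

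**5. Is the problem wider than empty arms?** Take true risks of 1% against 5%, 150 per arm, two-sided 5%, all tables enumerated. Wald rejects in 23.4% of trials if empty-arm tables count as non-rejections; Fisher rejects in 39.6%. About 22.2% of tables have an empty arm, and Fisher rejects there with total probability 17.0%. That leaves 39.6 − 17.0 = 22.7% (before rounding) for Fisher where both arms have deaths. Within those tables the rates are 23.4/77.8 = 30.1% for Wald and 22.7/77.8 = 29.1% for Fisher. The whole gap comes from the empty-arm tables.

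**The case against.** Four points can fairly be made against this.

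- **Wald inference is not written into the plan.** This stands. The article asks for a relative risk and 95% CI without naming the interval, and the same model's likelihood-ratio test and profile limit remain usable when the intervention arm is the empty one. What is left is that the usual output is not excluded, and that an empty control arm gives no finite relative risk by any of these routes.
- **A fallback for sparse events normally belongs in the analysis plan, which is not shown.** This lowers the weight of the point. It does not remove it, because the article fixes a model for a whole class of outcomes and exempts only continuous and repeated ones. Mortality is placed there by category, and the linking phrase is loose.
- **A reader might infer that a real difference in deaths would be reported as no evidence at all.** The documents do not support that. Counts and percentages are to be shown, deaths are reported as serious adverse events, adverse effects get a separate analysis in the safety population, and the DMEC section has results reviewed by masked arm. A standard error near 16,000 would also be noticed.
- **A reader might also infer that the method loses much power with only one or two deaths in an arm.** Step 5 does not bear this out: where both arms have deaths, Wald and Fisher reject about equally often.

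**Conclusion.** The point holds in a limited form and is minor. The written rule places mortality under a log-binomial relative risk without exempting rare outcomes, and that estimate is not finite on the log scale when an arm has no deaths. An empty arm is a realistic prospect if mortality is about 1% to 2% (63% to 18% for at least one of four) and unlikely at 3% or more (about 4% or less). These figures rest on an assumed mortality common to all arms and on 150 analysed per arm.

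The fault is confined to the planned model's p-value and interval, and essentially to tables with an empty arm. The 63% is the chance of any empty arm, mostly with no difference to hide. A significant Fisher result masked by Wald output has a probability of about 3% to 26% per contrast in the assumed scenarios with a true difference. The primary analysis and the sample size are unaffected.

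**What to change.** Add one or two sentences to Statistical methods {20a}. For mortality, and for any other single-measurement binary outcome with no or very few events in an arm, report events/n per arm, the unadjusted risk difference from control with a score-based (Miettinen-Nurminen) 95% CI, and an exact p-value. If a relative risk is also given, use a score or profile-likelihood interval, not a Wald interval.

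The cost is a few lines of code. The downside is that mortality would be shown without covariate adjustment and on a different scale from the primary outcome.
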